## Abstract

Mouthwashes containing cetylpyridinium chloride (CPC) or on-demand aqueous chlorine dioxide (ACD) have potential to reduce the salivary severe acute respiratory syndrome coronavirus 2 (SARS-CoV-2) load in individuals with SARS-CoV-2 infection. This study will evaluate the effect of CPC and on-demand ACD mouthwashes on salivary SARS-CoV-2 levels in individuals with acute asymptomatic or mild SARS-CoV-2 infection (COVID-19) staying in a residential recuperation facility in Osaka, Japan. This randomized, open-label clinical trial will include three equal-sized groups (CPC mouthwash, on-demand ACD mouthwash, and placebo), with 30 participants per group. A stratified replacement block method will be used to ensure balanced allocation based on symptom presence and days since symptom onset. Participants will use mouthwash at set times for 7 days or until the end of recuperation. Saliva samples will be collected at multiple time points and tested for SARS-CoV-2 using quantitative reverse transcription polymerase chain reaction. The primary outcome will be changes in salivary SARS-CoV-2 viral load 2 h after the first mouthwash use compared with the pre-mouthwash level. Secondary outcomes will include changes in salivary viral load and clinical parameters at different time points. This study was registered with the Japan Registry of Clinical Trials on 18 October 2022 (jRCTs051220107).

## 1. Introduction

Ever since the abrupt emergence of severe acute respiratory syndrome coronavirus 2 (SARS-CoV-2) in the People’s Republic of China, coronavirus disease 2019 (COVID-19) has left an indelible global footprint. This viral scourge has resulted in substantial morbidity, mortality, and significant economic ramifications.

COVID-19 infection involves the oral cavity, suggesting that saliva and the salivary glands potentially serve as sources for the transmission of the virus. Consequently, there has been a focus on investigating mouthwashes containing substances that exhibit virucidal activity, with the aim of preventing COVID-19 infection and mitigating the spread of the virus. Cetylpyridinium chloride (CPC) is a bactericide frequently used in mouthwashes, lozenges, and sprays [1]. In vitro studies have shown that CPC inactivates SARS-CoV-2 [2,3]. Because CPC disrupts lipid bilayers, high concentrations of CPC can have cytotoxic effects, but even low concentrations of CPC (0.001–0.005%) have been reported to inhibit the infectivity of SARS-CoV-2 Wuhan and the Alpha, Beta, and Gamma variants [1]. The antiviral effect is due to the denaturation of SARS-CoV-2 protein, rather than the disruption of lipid membranes [1]. Previous studies are limited by their small sample sizes. In a clinical study conducted in Singapore on patients with COVID-19, a reduction in the SARS-CoV-2 salivary viral load was observed 5 min and 6 h after using a CPC-containing mouthwash (four participants) compared with a control group (two participants) [4]. Although the sample size was small, CPC reduced the salivary SARS-CoV-2 viral load [5].

A novel mouthwash, MA-T^TM^ (developed by the Japan MA-T Industrial Association, Tokyo, Japan), was introduced to address the shortcomings of conventional chlorine dioxide solutions intended for human use. This mouthwash featured an on-demand aqueous chlorine dioxide (ACD) formulation [6]. In vitro studies have shown that chlorine dioxide and on-demand ACD have strong antiviral effects against SARS-CoV-2 [7], but no clinical studies have been conducted to date.

Based on previous clinical investigations, it is anticipated that CPC may attenuate the presence of SARS-CoV-2 in salivary specimens. However, this requires confirmation owing to the limited sample size in previous studies. The primary objective of this study is to assess the efficacy of CPC and on-demand ACD mouthwashes compared with a placebo at lowering the SARS-CoV-2 viral load in the saliva of individuals with mild or asymptomatic SARS-CoV-2 infection. If this investigation confirms the efficacy of mouthwashes containing CPC and on-demand ACD in mitigating SARS-CoV-2 levels in saliva, this could make a useful contribution to the prophylaxis of SARS-CoV-2 infection, and to transmission, especially in group settings.

Participant enrollment started in October 2022 and was completed in January 2023. As of October 2023, data analysis is in progress.

## 2. Experimental Design

This protocol was written in accordance with the Standard Protocol Items: Recommendations for Interventional Trials (SPIRIT) reporting template [8] (Supplementary Materials S1 file). This single-center, randomized (1:1:1), open-label clinical trial has three treatment groups: CPC mouthwash, on-demand ACD mouthwash, and placebo. A stratified replacement block method will be used for allocation. Allocation factors include the presence or absence of symptoms and the number of days elapsed since their onset (asymptomatic, within 3 days of onset, or ≥4 days since onset). All three groups will use a mouthwash or placebo from day 1 to day 7, until the last recuperation day or treatment discontinuation, whichever comes first.

### 2.1. Study Setting

This study will include patients with mild or asymptomatic SARS-CoV-2 infection who are recuperating at a specific hotel designated for COVID-19 treatment by the Osaka Prefecture health authority.

### 2.2. Eligibility Criteria

#### 2.2.1. Inclusion Criteria

Age ≥ 18 years;A confirmed COVID-19 diagnosis using nucleic acid amplification tests (reverse transcription polymerase chain reaction (RT-PCR), loop-mediated isothermal amplification (LAMP), or antigen tests), with or without mild COVID-19 symptoms ≤7 days after onset;Recuperating at a designated hotel in Osaka, Japan;No clinical contraindications for mouthwash use;Smartphone access with communication applications.

#### 2.2.2. Exclusion Criteria

A previously confirmed diagnosis of COVID-19, with or without hospitalization;An incipient need for hospitalization;Currently pregnant/breastfeeding;Receipt of antiviral or immunosuppressive medicines since the onset of COVID-19, including remdesivir, molnupiravir, nirmatrelvir/ritonavir, sotrovimab, casirivimab/imdevimab, anti-interleukin-6 receptor antibody, Janus kinase inhibitors, or corticosteroids.

### 2.3. Objectives

The primary objective of this study is to assess the efficacy of CPC and on-demand ACD mouthwashes compared with a placebo at lowering the SARS-CoV-2 viral load in the saliva of individuals with mild or asymptomatic SARS-CoV-2 infection.

#### 2.3.1. Primary Outcome

The primary outcome is the change in salivary SARS-CoV-2 viral load 2 h after the initial mouthwash application compared with that before the first mouthwash application.

#### 2.3.2. Secondary Outcomes

The secondary outcomes are:The change in salivary SARS-CoV-2 viral load 30 min after the initial mouthwash application compared with the baseline measurement;The change in salivary SARS-CoV-2 viral load 4 h after the initial mouthwash application compared with the baseline measurement;The change in salivary SARS-CoV-2 viral load 10 h after the initial mouthwash application compared with the baseline measurement;The change in salivary SARS-CoV-2 viral load 24 h after the first mouthwash application compared with the baseline measurement;The change in transcutaneous arterial blood oxygen saturation (SpO_2_) 24 h after the first mouthwash application (measured on the morning of day 2) compared with the baseline measurement;The change in the clinical condition rating scale 24 h after the first mouthwash application (measured on the morning of day 2) compared with the baseline measurement;The change in SpO_2_ 7 days after the first mouthwash application (measured on the morning of day 7) or on the last recuperation day, compared with the baseline measurement;The change in the clinical condition rating scale 6 days after the first mouthwash application (measured on the morning of day 7 of mouthwash use) or on the last recuperation day, compared with that before the first mouthwash application.

### 2.4. Sample Size

A parallel, 3-group design will be used. The hypotheses will be evaluated using two-sided, two-sample, Bonferroni-adjusted, unequal-variance (Welch’s) *t*-tests, with an overall Type I error rate (α) of 0.05. The group standard deviations (beginning with the control group) will be assumed to be 1, 1, and 1. The control group mean will be assumed to be 0. To detect a mean reduction in salivary viral load of 90% in participants using mouthwash, with at least 80% power for each test, the sample size needed for each of the three groups (calculated using PASS 2022) is 25. Considering the feasibility and the possibility of some participants not completing the intervention, the target sample size is 30 cases per group.

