### 2.5. Statistical Methods

Where applicable, the baseline participant characteristics will be presented as frequencies and proportions (%) for categorical data and the median and interquartile range (IQR) for continuous data. Linear mixed-effects models will be used to evaluate the effect of the CPC and ACD mouthwashes on salivary SARS-CoV-2 viral load compared with a placebo. As the study interventions are considered low-risk interventions, no interim analyses are planned. No subgroup analyses or additional analyses are planned. The statistical tests will be two-tailed and a value of *p* < 0.05 will be considered to indicate statistical significance. All analyses will be performed using Stata 18.0 (StataCorp LLC, College Station, TX, USA).

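### Sections 2.4 and 2.5 give different significance thresholds for the two mouthwash-placebo contrasts; one Holm rule in both would keep the 5% family-wise error and gain modest power if both products work

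*Protocol article*

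**What the plan says.** The aim in Section 2.3 is to assess both the CPC and the ACD mouthwash against placebo. The primary outcome is the change in salivary viral load at 2 h.

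Section 2.4 bases the sample size on "two-sided, two-sample, Bonferroni-adjusted, unequal-variance" Welch t-tests, "with an overall Type I error rate (α) of 0.05". The other inputs are:
- effect: "To detect a mean reduction in salivary viral load of 90% in participants using mouthwash"
- spread: "The group standard deviations (beginning with the control group) will be assumed to be 1, 1, and 1"
- control mean: "The control group mean will be assumed to be 0"
- power: "with at least 80% power for each test"
- result: "the sample size needed for each of the three groups (calculated using PASS 2022) is 25", raised to a target of 30

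Section 2.4 does not state the number of comparisons or the scale of the 90% reduction. It sets no power target for showing that both products work.

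Section 2.5 evaluates both mouthwashes against placebo with linear mixed-effects models. Its sentence beginning "The statistical tests will be two-tailed and a value of" sets the threshold at p < 0.05. It mentions no multiplicity adjustment.

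**The concern.** The two sections differ on the test and on the threshold for the same primary question. If each contrast is judged at 0.05 as Section 2.5 reads, the overall 5% of Section 2.4 is lost. If plain Bonferroni governs, the error rate is held, but some power is given up that a step-down version would keep at no cost in error rate or participants.

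That power matters most for the second product when both work. Section 6 draws a separate practical conclusion for each mouthwash, so a verdict on each one counts. Since the threshold in Section 2.5 has to be clarified anyway, this is the natural place to choose the more efficient rule.

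**Working it through.** **1. Reproduce the 25 per group.** Inputs from Section 2.4: SD 1 in each group, two-sided tests, overall alpha 0.05, 80% power per test. Assumptions: two comparisons, so alpha per test = 0.05/2 = 0.025, and a difference of 0.9 SD. With equal n and SD, the noncentral t is a close stand-in for Welch:

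- noncentrality = d / sqrt(2/n) = 0.9 / sqrt(2/25) = 3.18, with 48 df and critical value 2.314
- power = 80.4% at n = 25, and 78.5% at n = 24

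So 25 is reproduced exactly. Other readings do not match it exactly: 1.0 SD with two comparisons needs 21 per group; with three comparisons, 0.9 SD needs 28 and 1.0 SD needs 23. On a log10 scale a 90% reduction is 1.0, so both 0.9 and 1.0 SD are carried forward.

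**2. Family-wise error when neither product works.** Three normal groups with SD 1 and Welch tests sharing the placebo arm were simulated, with 400,000 trials per setting.

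- Both tests at 0.05: each rejects in 5.0% of trials and both reject in about 0.9%, so at least one rejects in about 5.0 + 5.0 − 0.9 = 9.1%.
- Bonferroni and Holm: about 4.6% each. They agree because Holm's first step is the Bonferroni test of the smaller p-value.

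**3. Power when both products have the same effect (same simulation).**

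| Effect (SD) | n per group | Per test, Bonferroni → Holm | Gain | Both shown, Bonferroni → Holm | Gain |
|---|---|---|---|---|---|
| 0.9 | 25 | 80.4% → 85.2% | 4.8 | 69.2% → 78.8% | 9.6 |
| 0.9 | 30 | 87.8% → 91.4% | 3.7 | 79.9% → 87.2% | 7.3 |
| 1.0 | 25 | 88.4% → 92.0% | 3.6 | 80.9% → 88.0% | 7.1 |
| 1.0 | 30 | 93.9% → 96.1% | 2.3 | 89.4% → 93.9% | 4.5 |

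Gains are in percentage points, taken before rounding. As a check, Holm adds a rejection only when one p-value is at most 0.025 and the other lies between 0.025 and 0.05. With equal effects, the per-test gain should therefore be half the gain for both: 9.6/2 = 4.8 and 4.5/2 = 2.25, which agrees.

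**4. Power when only one product works.** The effective product gains about 0.2 points (at 0.9 SD and n = 25, 80.3% → 80.5%). False rejection for the ineffective product rises from about 2.5% to between 4.3% and 4.7%, still within 5%. Power to show at least one product is unchanged in every setting.

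**5. If three pairwise comparisons were meant.** Over the same effects and n = 25 to 30, Holm's gains are about 2 to 3 points per test and 4 to 7 points for both mouthwash-placebo contrasts.

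**The case against.** The strongest reply is that nothing in Section 2.4 is wrong. Bonferroni is valid, the stated target is power for each test, and it is met: 80.4% at 25 per group and about 88% at 30 for 0.9 SD. Power to show both products is not a target the protocol sets. All of this stands. A reader might infer that the sample size is faulty or that the trial is underpowered; the documents support neither.

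A reader might also take the gain of about 5 points per test as general. It belongs to 0.9 SD and 25 per group with both products fully effective. At 30 per group and 1.0 SD it is 2.3. Section 6 bases its expectation on earlier clinical results for CPC only, and the Introduction reports no clinical study of ACD, so equal effects are not the documented expectation.

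Next, if Section 2.5 governs as written, each contrast is tested at 0.05 and Holm tightens the rule. That is correct, but the tightening is what the overall 5% of Section 2.4 requires. It costs little for showing both: at 0.9 SD and 30 per group, 87.2% with Holm against 87.7% unadjusted. Section 2.5 could also mean 0.05 for already adjusted p-values. The text does not say, so it would be wrong to conclude that multiplicity control has been dropped. Repeating Bonferroni in Section 2.5 would also settle the threshold; Holm does so with more power.

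Two costs are real. Every extra Holm rejection has a p-value between 0.025 and 0.05, so the 97.5% interval for that contrast includes zero. And the trial is open-label, enrollment ended in January 2023 and analysis was in progress by October 2023, so a late move to a rule that rejects more often needs protection. Both narrow the recommendation without defeating it.

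**Conclusion.** The point holds as a discrepancy to reconcile plus an inexpensive efficiency gain. The thresholds in Sections 2.4 and 2.5, taken literally, imply family-wise errors of at most 5% and about 9%. Holm settles this at 5%, and its power is never below Bonferroni's, so the 25 per group stands.

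The 2 to 5 points per test and 4.5 to 10 points for both rest on two comparisons, Welch tests, and effects of 0.9 to 1.0 SD in both mouthwash groups. If the reconciled plan uses the mixed model, Holm's error control carries over to any valid p-values, but these power figures do not transfer directly.

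**What to change.** State one primary rule, in the same words, in Sections 2.4 and 2.5: the CPC-placebo and ACD-placebo contrasts at 2 h are tested with Holm's procedure at an overall two-sided alpha of 0.05, the smaller p-value against 0.025 and, if that is significant, the other against 0.05. Apply it to whichever test, Welch or mixed model, the reconciled plan names as primary; that choice must be settled separately. Also state that there are two comparisons.

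If Bonferroni 97.5% confidence intervals are reported, label them as not matching the Holm test, since they can include zero for the second rejected contrast.

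The change takes about a sentence in each section and needs no extra data or participants. Its main cost is credibility: it must be dated and documented before anyone sees results by arm. If those results have already been seen, keep Bonferroni as the primary rule and state it in Section 2.5.

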### 2.5. Statistical Methods

Where applicable, the baseline participant characteristics will be presented as frequencies and proportions (%) for categorical data and the median and interquartile range (IQR) for continuous data. Linear mixed-effects models will be used to evaluate the effect of the CPC and ACD mouthwashes on salivary SARS-CoV-2 viral load compared with a placebo. As the study interventions are considered low-risk interventions, no interim analyses are planned. No subgroup analyses or additional analyses are planned. The statistical tests will be two-tailed and a value of *p* < 0.05 will be considered to indicate statistical significance. All analyses will be performed using Stata 18.0 (StataCorp LLC, College Station, TX, USA).

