#### Mouthwash Application Method

Eligible patients will be randomly assigned to groups and will be instructed to use specific mouth rinses as follows: a 20 mL placebo solution (consisting of purified water) for 1 min, a 20 mL mouthwash containing 0.05% CPC for 30 s, or a 10 mL mouthwash with 0.01% on-demand ACD for 1 min. This regimen will be followed for 7 days. A baseline saliva sample will be collected before initiating the mouthwash regimen. Following the sample collection, patients will rinse their mouths with the assigned mouthwash or placebo. Six saliva samples will be collected at the following time points: baseline (immediately before breakfast at 08:00), 30 min after baseline (08:30), 2 h after baseline (10:00), 4 h after baseline (immediately before lunch at 12:00), 10 h after baseline (immediately before dinner at 18:00), and 24 h after baseline (immediately before breakfast the following morning at 08:00).

After each saliva sample collection, participants will be instructed to rinse their mouths with the allocated mouthwash or water at baseline and again at the 4, 10, and 24 h time points. The saliva samples will be individually collected in sterile tubes at the hotel, inactivated, and stored at 4 °C in a refrigerator at Osaka University. The saliva samples will then be sent to the Research Foundation for Microbial Diseases of Osaka University (BIKEN), and RT-PCR testing for SARS-CoV-2 will be conducted within 36 h of sample collection. Saliva collected according to this research protocol will be stored in a freezer at −80 °C in the laboratory of Infection Control, Osaka University Graduate School of Medicine for one year after study completion.

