## 4. Data Collection and Management

### 4.1. Plans for Assessment and Collection of Outcomes

The timing of outcome assessments is shown in Table 1. Saliva will be collected for SARS-CoV-2 viral load measurement at baseline and 30 min, 2 h, 4 h, 10 h, and 24 h after first mouthwash application. SpO_2_ will be measured in the morning at baseline and on days 2 and 7 of mouthwash use. If mouthwash use is discontinued within 7 days, SpO_2_ will be measured in the morning of the day of discontinuation instead of on day 7. The clinical condition rating scale will be administered at baseline and on days 2 and 7 of mouthwash use. If mouthwash use is discontinued within 7 days, the clinical condition rating scale will be administered on the day of discontinuation instead of on day 7.

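### The article does not say whether Welch t-tests (Section 2.4) or mixed models (Section 2.5) test the 2 h primary outcome, or at what significance threshold

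*Protocol article*

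**What the plan says.** Section 2.3.1 of the protocol article fixes one time point: "The primary outcome is the change in salivary SARS-CoV-2 viral load 2 h after the initial mouthwash application", compared with the level before the first rinse. Section 2.3.2 lists the changes at 30 min, 4 h, 10 h and 24 h as four separate secondary outcomes.

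Two sections then describe how the effect is tested.

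- Section 2.4 (Sample Size): "The hypotheses will be evaluated using two-sided, two-sample, Bonferroni-adjusted, unequal-variance" (Welch) t-tests, with an overall Type I error rate of 0.05.
- Section 2.5 (Statistical Methods): "Linear mixed-effects models will be used to evaluate the effect of the CPC and ACD mouthwashes on salivary SARS-CoV-2 viral load", with placebo as the comparator. Tests are two-tailed and read at p < 0.05. No additional analyses are planned.

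The data for a mixed model are repeated samples. According to Section 4.1, "Saliva will be collected for SARS-CoV-2 viral load measurement at baseline and 30 min, 2 h, 4 h, 10 h, and 24 h". Under Mouthwash Application Method, participants rinse after sampling "at baseline and again at the 4, 10, and 24 h time points". Section 3.3 states that the trial is open-label. The Introduction says: "As of October 2023, data analysis is in progress".

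**The concern.** Each of the two sentences, read alone, states how efficacy will be tested. They differ in three respects.

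- **Method:** a two-sample t-test against a mixed model.
- **Threshold:** Bonferroni-adjusted in Section 2.4, a plain p < 0.05 in Section 2.5.
- **Link to the primary outcome:** the t-test fits a change at a single time point. The mixed-model sentence speaks of an effect on viral load and names no time point or contrast.

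Section 2.5 plans nothing beyond what it lists, so the t-test cannot be taken as an announced supporting analysis. No other section reconciles the two.

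What is at stake is pre-specification. With allocation known and analysis under way, more than one test can be defended from the text as the primary one. A reader of the results could not tell from this article whether the test reported was the one fixed in advance.

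**Working it through.** **1. What the stated sample size belongs to.** The inputs from Section 2.4 are SD 1 in each group, control mean 0, a 90% reduction, at least 80% power per test and overall two-sided alpha 0.05. The number of comparisons is not stated. Two (each active arm against placebo) is assumed here, giving 0.05/2 = 0.025 per test. Power comes from the noncentral t with 2n - 2 degrees of freedom and noncentrality d / (SD × √(2/n)).

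- d = 0.9: n = 24 gives power 0.785 and n = 25 gives 0.804, so the stated 25 is reproduced exactly.
- d = 1.0 (90% as 1 log10): 21 per group suffices. Power is 0.885 at n = 25 and 0.939 at n = 30.

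The 25 is therefore the size for a comparison at one time point by t-test with two Bonferroni-adjusted comparisons. That agrees with the 2 h outcome and with 0.025 per test. Section 2.5 carries over neither.

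**2. The threshold.** Taken literally, Section 2.5 allows each of two comparisons at 0.05. The family-wise error is then 1 - 0.95² = 0.0975 if the two are independent, and about 0.090 when they share a placebo arm (correlation 0.5). Section 2.4 promises 0.05 overall.

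**3. What a free choice of test would cost.** Suppose the two candidates are the 2 h change and the mean of the five post-baseline changes, each change with SD 1 and a common correlation ρ between changes. The documents give no ρ, so 0.3, 0.5 and 0.7 are assumed. The mean has variance (1 + 4ρ)/5, and its correlation with the 2 h change is √((1 + 4ρ)/5). With no true effect and each test at 0.025, the chance that at least one is significant is 0.025 + 0.025 - P(both), with P(both) from the bivariate normal.

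| ρ | correlation of the two tests | P(both) | P(at least one) |
|---|---|---|---|
| 0.3 | 0.66 | 0.0062 | 0.0438 |
| 0.5 | 0.77 | 0.0090 | 0.0410 |
| 0.7 | 0.87 | 0.0125 | 0.0375 |

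The error per comparison is thus about 3.8 to 4.4% where 2.5% was intended.

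**4. How far the two candidates could differ.** The table shows power at n = 30 and 0.025, for assumed effects in log10 units at 30 min, 2, 4, 10 and 24 h. In every row the 2 h effect is 1.0, so the 2 h test has power 0.94.

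| assumed effect | average | power of averaged test, ρ = 0.3 / 0.5 / 0.7 |
|---|---|---|
| 1, 1, 1, 1, 1 | 1.00 | 1.00 / 0.996 / 0.98 |
| 1, 1, 0.5, 0.25, 0 | 0.55 | 0.82 / 0.67 / 0.56 |
| 1, 1, 0, 0, 0 | 0.40 | 0.52 / 0.39 / 0.31 |

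The tests agree in what they estimate only if the effect is constant over time. In that case averaging loses nothing. The later samples also reflect more rinsing: with rinses after the baseline, 4 h and 10 h samples, the 10 h sample follows two rinses and the 24 h sample three.

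**The case against.** The strongest reply is that Section 2.4 is a sample size section. Its t-test sentence stands beside the assumed SDs and the named software and can be read as the basis of the calculation only. Section 2.5 is the analysis section and names one method. Planning on a t-test and analysing by mixed model is ordinary practice. This stands, and the difference in method alone would not be a fault. It does not dispose of the point, because Section 2.4 says the hypotheses will be evaluated that way, and Section 2.5 drops both the time point and the adjustment without comment.

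A second reply is that model details belong in an analysis plan or full protocol that is not shown. That holds for covariance structure and covariates, and their absence is no criticism here. It does not cover two sentences of one article that disagree on the test and its threshold.

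A reader might go further and infer that the trial has two declared primary analyses, or that it will test an effect averaged over 24 h. The documents do not support either. Neither section uses the term primary analysis. Sections 2.3.1 and 2.3.2 define every viral-load outcome at its own time point, and no average is listed, which favours contrasts by time point. The averaged effect is a model that the wording would permit, not one the plan states.

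Nor do the documents show that the choice was left open in practice. Registration and ethics approval date from October 2022, and the approved protocol is not shown.

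**Conclusion.** The point holds as an unresolved conflict: the article does not say which method tests the 2 h outcome, or whether the threshold per comparison is 0.025 or 0.05. The wording and the missing reconciliation can be read directly and need no assumption.

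The size is conditional. The error of 3.8 to 4.4% per comparison assumes a choice between exactly two tests, both at 0.025, and correlations of 0.3 to 0.7. The power figures for an averaged test rest on assumed time profiles and range from no loss under a constant effect to a large loss under a short-lived one. They show why the contrast should be named and do not predict what this trial will do. The sample size is not undermined: a 2 h contrast at 0.025 has power 0.94 at 30 per group for a 1 log10 difference with SD 1.

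**What to change.** In Section 2.5, state that the primary analysis is a linear mixed model for log10 viral load with group, categorical time and group-by-time interaction. State that the primary tests are the CPC-placebo and ACD-placebo contrasts for change from baseline at 2 h, each at the Bonferroni level implied by Section 2.4 (0.025 for two comparisons). Name the contrasts at the other time points as secondary.

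In Section 2.4, say that the Welch t-test is the basis of the sample size only, or name it as a sensitivity analysis for the 2 h change.

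The cost is a few sentences, with the same data and software. Because analysis was already in progress when the article was written, add a dated statement of when the primary test was fixed and whether any results had been seen by then. If the approved protocol or an analysis plan already fixes it, citing that document and its date is enough.

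### Section 2.5 does not carry over the Bonferroni adjustment promised in section 2.4; if p < 0.05 is applied to raw p-values, the two primary contrasts have a family-wise error of about 9.1%, not 5%

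*Protocol article*

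**What the plan says.** Section 2.4 (Sample Size) states the testing rule in the future tense, as a commitment about the analysis: "The hypotheses will be evaluated using two-sided, two-sample, Bonferroni-adjusted, unequal-variance" t-tests, "with an overall Type I error rate (α) of 0.05". It plans for power "with at least 80% power for each test" and arrives at 25 per group, raised to a target of 30.

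Section 2.5 (Statistical Methods) names a different analysis: "Linear mixed-effects models will be used to evaluate the effect of the CPC and ACD mouthwashes on salivary SARS-CoV-2 viral load compared with a placebo". It then gives the significance rule: "The statistical tests will be two-tailed and a value of *p* < 0.05 will be considered to indicate statistical significance". It mentions no adjustment, hierarchy or gatekeeping, and multiplicity comes up nowhere else in the article.

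Section 2.3 sets the objective, to "assess the efficacy of CPC and on-demand ACD mouthwashes compared with a placebo", which makes two comparisons against one control arm. Section 2.3.1 names one primary outcome at one time: "The primary outcome is the change in salivary SARS-CoV-2 viral load 2 h after the initial mouthwash application".

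**The concern.** The two sections can give different answers for the same data. The adjustment in section 2.4 is attached to Welch t-tests, and section 2.5 drops those tests. An analyst working from section 2.5 would take the two treatment contrasts from the mixed model and compare each p-value with 0.05. An analyst working from section 2.4 would require 0.025 for each.

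This matters because either product can succeed alone. Section 6 (Expected Results) describes a separate consequence for each mouthwash if it is shown to work. With two chances of a positive claim, the overall error rate is the property at stake, and the protocol itself chose to hold it at 0.05.

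**Working it through.** **Inputs.** From section 2.4: overall two-sided alpha 0.05, Bonferroni, SD 1 in each group, control mean 0, at least 80% power per test, 25 per group. From sections 2.3 and 2.3.1: two active-versus-placebo comparisons on one primary outcome. From section 2: 1:1:1 allocation. Section 2.4 does not state the number of comparisons in the Bonferroni family; two is inferred from the objective. The effect is given as a 90% reduction ("To detect a mean reduction in salivary viral load of 90% in participants using mouthwash") with no scale, so two values are used: a difference of 0.9 (the percentage entered as a number) and 1.0 (90% is one unit on the log10 scale). Both are assumptions.

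**Step 1: reproduce the stated 25.** The normal approximation is n = 2(z₁₋α/₂ + z₀.₈₀)² / d², with SD 1.

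- d = 0.9, alpha 0.025: 2(2.2414 + 0.8416)² / 0.81 = 23.5, so 24.
- d = 0.9, alpha 0.05: 2(1.9600 + 0.8416)² / 0.81 = 19.4, so 20.

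The noncentral t calculation (equal n and SD, so practically the same as Welch; noncentrality d/√(2/n), 2n − 2 df) gives the smallest n with at least 80% power:

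| Difference | alpha 0.05 | alpha 0.025 | alpha 0.05/3 |
|---|---|---|---|
| 0.9 SD | 21 | **25** | 28 |
| 1.0 SD | 17 | 21 | 23 |

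The stated 25 is matched exactly at 0.9 SD with 0.025 per comparison (power 80.4%). Unadjusted testing gives 21 or 17 at these two differences, not 25. This supports the view that an adjustment was built into the sample size.

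**Step 2: family-wise error for the two primary contrasts.** With equal arms, each contrast has variance 2σ²/n and the two share the placebo variance σ²/n. Their correlation is therefore (σ²/n)/(2σ²/n) = 0.5. Under the global null:

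- 0.05 each: 1 − P(|Z₁| < 1.960, |Z₂| < 1.960) = 0.0907.
- 0.025 each: 1 − P(|Z₁| < 2.2414, |Z₂| < 2.2414) = 0.0465.

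For comparison, if the contrasts were independent, 1 − 0.95² = 0.0975 and 1 − 0.975² = 0.0494. The upper bound for two tests at 0.05 is 0.10. A Welch simulation with 400,000 runs gave 8.9% at 25 per group and 9.1% at 30 for tests at 0.05, and 4.6% at both sizes for tests at 0.025.

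**Step 3: power per comparison if the adjustment is kept.**

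| n per group | Difference | alpha 0.05 | alpha 0.025 |
|---|---|---|---|
| 25 | 0.9 SD | 87.7% | 80.4% |
| 25 | 1.0 SD | 93.4% | 88.5% |
| 30 | 0.9 SD | 92.9% | 87.9% |
| 30 | 1.0 SD | 96.8% | 93.9% |

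**The case against.** The strongest reply is that the sections are compatible. Section 2.5 never says its p-values are unadjusted. Bonferroni-adjusted p-values are by construction compared with 0.05, and section 2.4 has already said that the hypotheses will be evaluated with adjustment. The article is also condensed, and how Bonferroni is applied inside a mixed model is a detail that an analysis plan may settle.

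Part of this stands. A reader might infer that the trial has abandoned error control, or that the two sections cannot both hold. The text does not support that: it is silent on whether the adjustment persists, and silence is not a rejection. What the reply does not remove is that section 2.5 changes the test to which the adjustment was attached and then states a general threshold without it. Taken at face value, the two sections decide a raw p-value between 0.025 and 0.05 differently. That is a problem in rules the article does state, not a complaint that detail is missing.

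Two further inferences should be resisted.

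- A reader might say that 25 can arise only from 0.025 per comparison. That holds only if the difference was 0.9 SD. At 1.0 SD, 0.025 needs 21, and 25 can also come from 0.05/3 with a difference of about 0.95 SD.
- A reader might extend the error calculation to all saliva time points and clinical outcomes. Section 2.4 does not clearly place secondary outcomes in the Bonferroni family, so leaving them unadjusted contradicts nothing. Any such figure would also need correlations between time points that the article does not give.

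**Conclusion.** The point holds as a conflict between the promised error control and the analysis rule as written, limited to the two primary contrasts. If p < 0.05 is applied to raw p-values, the family-wise error is about 9.1% instead of 5%. That figure assumes the global null, equal arms sharing one placebo group, and exactly two comparisons; it does not depend on the effect size or SD. If section 2.5 was meant to refer to Bonferroni-adjusted p-values, the error rate is about 4.6% and only the wording is at fault.

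The match of 25 per group to 0.025 per comparison is supporting evidence, conditional on a difference of 0.9 SD. The conflict does not rest on it.

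**What to change.** Add to section 2.5: each of the two active-versus-placebo contrasts for the 2 h primary outcome, estimated from the mixed model, is tested two-sided at 0.025; equivalently, Bonferroni-adjusted p-values are compared with 0.05. State that p < 0.05 for secondary outcomes is outside this family-wise control. Naming the mixed-model contrast as the primary test also settles which analysis replaces the Welch tests of section 2.4.

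The cost is a sentence or two and no extra participants. Power per comparison stays above the planned 80%, although at 25 per group and 0.9 SD it is 80.4%, with almost no margin; the target of 30 gives 87.9%. Because the introduction reports enrolment complete and analysis in progress as of October 2023, the clarification should be recorded before the results are interpreted. It restores a rule that section 2.4 already states, so it need not look like a choice made after seeing data.
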